## Abstract

**Introduction:** Parkinson's disease (PD) is one of the most frequent causes of disability among older people, characterized by motor disorders, rigidity, and balance problems. Recently, dance has started to be considered an effective exercise for people with PD. In particular, Irish dancing, along with tango and different forms of modern dance, may be a valid strategy to motivate people with PD to perform physical activity. The present protocol aims to implement and evaluate a rehabilitation program based on a new system called “SI-ROBOTICS,” composed of multiple technological components, such as a social robotic platform embedded with an artificial vision setting, a dance-based game, environmental and wearable sensors, and an advanced AI reasoner module.

**Methods and Analysis:** For this study, 20 patients with PD will be recruited. Sixteen therapy sessions of 50 min will be conducted (two training sessions per week, for 8 weeks), involving two patients at a time. Evaluation will be primarily focused on the acceptability of the SI-ROBOTICS system. Moreover, the analysis of the impact on the patients' functional status, gait, balance, fear of falling, cardio-respiratory performance, motor symptoms related to PD, and quality of life, will be considered as secondary outcomes. The trial will start in November 2021 and is expected to end by April 2022.

**Discussions:** The study aims to propose and evaluate a new approach in PD rehabilitation, focused on the use of Irish dancing, together with a new technological system focused on helping the patient perform the dance steps and on collecting kinematic and performance parameters used both by the physiotherapist (for the evaluation and planning of the subsequent sessions) and by the system (to outline the levels of difficulty of the exercise).

**Ethics and Dissemination:** The study was approved by the Ethics Committee of the IRCCS INRCA. It was recorded in ClinicalTrials.gov on the number NCT05005208. The study findings will be used for publication in peer-reviewed scientific journals and presentations in scientific meetings.

## Introduction

Parkinson's disease (PD) is one of the most frequent causes of disability among older people. According to the Parkinson's Foundation, more than 10 million people worldwide are living with PD^1^. PD is a chronic-progressive neuro-degenerative disease, characterized by motor disturbances such as bradykinesia (poor and slow movement), tremor at rest, rigidity, posture in flexion and “shuffling gait,” and, not least, a lack of balance resulting in a high risk of falling (1–4). Balance disorders do not always respond to the dopaminergic therapy used in PD. Therefore, physiotherapy becomes an important intervention for their management (5, 6). Postural instability and the resulting falls are among the main factors leading to poorer quality of life, morbidity, and increased mortality risk for people with PD (7). These pathological conditions are routinely treated by rehabilitation approaches aimed at improving static/dynamic balance, recovering walking ability, and preventing falls (3, 8).

Recently, dance has started to be considered as effective training for people with PD, especially for those at the initial stage of PD and with mild/moderate disease severity (9, 10). It has been shown that dance in people with PD can have a positive effect on balance and mobility and can help improving quality of life by reducing symptoms of depression (11–14). Recent studies have shown that sometimes dance can improve balance and functional mobility (15, 16).

Irish dancing, along with tango and other forms of modern dance, may be a valid strategy to motivate people with PD to perform physical activity. Recent studies have shown that Irish dancing can improve balance, mobility, and quality of life through the integration of complex learning patterns of motor skills, dynamic balance, musicality, and socialization (17–20). In addition, Irish music, due to its rhythm, has a predictable pattern that can improve gait and walking (18).

A recent review of the literature (21) pointed out the relevance of different types of dance for improving motor and non-motor symptoms in PD. Despite limited evidence, this review highlights an improvement in motor function, freezing, balance, and gait, as compared to physiotherapy, in people with PD who underwent Irish dance intervention.

In a recent study (22), the researchers have examined the feasibility of a randomized controlled study design and the benefits of an Irish dancing-based intervention, with 90 patients with idiopathic PD. The participants were randomized to Irish set dance classes or to a usual care group. The dance group attended a 1.5-h dancing class each week, for 10 weeks and undertook a home dance program for 20 min, 3 times per week. The usual care group has followed usual care and daily activities. The results have shown that, in the case of mild to moderately severe PD, the Irish dance is a feasible and enjoyable strategy to improve patients' quality of life.

Besides highlighting the positive impact of dancing, several studies have also tried to assess the impact of robot dancers to support older people (23), especially with PD (24). In comparison to human–human partner dance, robot dance partners may support the collection of objective health parameters during the performance, allowing the customization on the basis of the older people's needs and preferences. Furthermore, robot dance partners potentially complement human–human dance by giving the opportunity of also training alone (25).

Moreover, a recent study (26) has demonstrated the acceptability and feasibility of a dancing intervention such as a robot as a partner. The results of this study underline that the 16 older dancers perceived the robot as useful, easy to use, and fun, suggesting a positive attitude toward the system and thus the intervention, evaluated through the Technology Acceptance Model (TAM) scale (27), a specific tool to assess and predict user acceptance of information systems and information technology. The authors have highlighted the need of increasing the complexity of dance exercises with the robot, to favor the engagement of the older dancers.

In line with the literature in the field, the main objective of this paper is to present the protocol for the “SI-ROBOTICS” intervention, aimed at assessing the acceptability of an innovative robotics-based system for engaging patients with Parkinson's disease in an Irish set dancing intervention.

## Methods and Analysis

### Trial Design

The study is designed as a technical feasibility pilot to test the SI-ROBOTICS system on a group of 20 older people with PD at an early stage (Hoen and Yahr Scale 1–2), during an Irish set dancing training. Assessment will be performed at the baseline (T0), after 4 weeks (mid-T1), and after 8 weeks of intervention (end-T2).

The primary aim is to evaluate the acceptability of the SI-ROBOTICS system in a group of patients with PD while performing a rehabilitation treatment based on Irish dancing, using the Unified Theory of Acceptance and Use of Technology (UTAUT) scale (28).

The secondary aim is the analysis of the modification of dimensions related to the general functional status, in terms of gait, balance, fear of falling, cardio-respiratory performance, motor symptoms related to PD, and quality of life.

### Study Setting

This study will be conducted at the Clinical Unit of Physical Rehabilitation of the Istituto Nazionale Ricovero e Cura per Anziani IRCCS INRCA, Ancona, Italy. The last version (second version) of the current protocol is dated May 25, 2021.

### Participants

The inclusion criteria will be:

Aged 65 and over;Capacity to consent;Hoen and Yahr scale: 1–2 stage;Functional Ambulation Category (FAC) ≥ 2;Rankin Scale score ≤ 3;Stability of drug treatment for at least 1 month;Geriatric Depression Scale 4-items ≤ 1;Mini Mental State Examination ≥ 24;Maintaining an upright posture ≥ 30, evaluated by a trained physiotherapist during the recruitment.

The exclusion criteria will be:

Failure to meet the inclusion criteria;Concomitant participation in other studies;Lack of written informed consent;History of syncopal episodes, epilepsy, and vertigo not controlled pharmacologically;Serious dysfunction of the autonomic system;Severe behavioral syndromes not compensated by drugs;Concurrent neurological and/or cardiac diseases;Recent femur fracture;Chronic medium to severe pain affecting standing or walking.

### Recruitment

Patients will be selected by the outpatient department at the Clinical Unit of Physical Rehabilitation, of IRCCS INRCA, in the Ancona branch. These patients will be contacted to schedule a visit with the clinical team. Once the compliance with the inclusion and exclusion criteria of the study will be verified and the informed consent will be obtained, the doctor will proceed with the baseline evaluation and with the acquisition of gait assessment parameters through G-walk sensor. The trial will start in November 2021 and is expected to end in April 2022.

### Intervention

For this study, 20 patients with PD will be enrolled. Sixteen therapy sessions of 50 min will be conducted (two training sessions per week, for 8 weeks), involving two patients at a time. Cardiac and respiratory activity monitoring will be conducted during dancing treatments in order to detect heart rate and breathing frequency. Participants will have to complete at least 80% of the sessions.

Each session will involve the following activities:

breathing, relaxation, and postural harmonization exercises (5 min);active mobility and stretching exercises (5 min);Irish dancing with the SI-ROBOTICS system (35 min);relaxation exercises (5 min).

### Platform Description

The SI-ROBOTICS system is composed of multiple technological components. Usability and acceptability of the single components have been evaluated singularly before the system integration. These components are:

**A robotic platform:** a social robot that will motivate the participants during the sessions, equipped with the Inter Real Sense camera, able to collect information on kinematic parameters such as position of pressure center in relation to the support base, steps, and body symmetry.**The let's dance game**: a serious game based on the choreography and a personalized avatar which will guide the participants to perform the dance sessions.**Wearable wellness system sensorized shirt:** to collect data on the patient's main clinical parameters (e.g., heart rate, breathing frequency, etc.) during the performance. These data will allow to collect the patient's performance data during the execution of tasks.

In addition, the system is constituted by:

**The AI reasoner module**: the backend intelligent part of the SI-ROBOTICS system that will allow the adaptation of the dance sessions, based on the users' performance and the data collected through the sensors. In this way, it will be possible to dynamically customize the session according to the user's needs and abilities.**The artificial vision setting**: a commercial camera called Inter Real Sense, installed in the experimental setting for the extraction of kinematic parameters. To extract features of interest from the signals, proprietary skeleton tracking software of the Real Sense camera will be used, together with specially developed algorithms for feature extraction.

Figures 1A,B shows the experimental setting in a protected environment (gymnasium) and the positioning of the technologies, the user and the physiotherapist, during the training sessions. In particular, the two participants will be placed in front of the screen and the central camera at a distance of 3.40 m. The robot and the physiotherapist will be positioned laterally, at a distance of 3 m. The robot will move without entering the blue area drawn in Figure 1B, using the navigation algorithm based on literature (29, 30).

**Figure 1 F1:**
[figure not shown]
SI-ROBOTIC system **(A)**. Expermental setting **(B)**.

The technical components are described in details in the following paragraphs.

#### Robotic Platform

From a technical point of view, the SI-ROBOTICS robot is composed of the MoVeR1 robotic platform (Co-Robotics, Italy) as shown in Figure 2, a two-axle autonomous vehicle with two front driving wheels and two rear omni-drive wheels, and an external cover, whose customized design was realized in collaboration with the Department of Design of the University of Genova.

**Figure 2 F2:**
[figure not shown]
SI-ROBOTICS platform.

The platform has been equipped with the following commercial sensors to be compliant with the scenario requirement:

- a microphone and a speaker to interact with the participants;- a tablet, providing a web interface to support the interaction during the service;- an Intel RealSense D435i RGB-D camera (Intel, USA), which helps the patient–robot interaction, measuring movements, and which performs the remote plethysmography service, by real-time measurement of heart rate and breath rate (31, 32);- a SICK TIM781 laser 2D, able to detect obstacles and people in the environment.

The robot software is based on the Robot Operating System (ROS) (33), which performs middleware function, i.e., connection layer of all software components strictly related to the robot operation. Among the relevant modules built on ROS, the autonomous navigation module is devoted to performing motor control, avoiding obstacles, planning the best paths, and so on. Furthermore, for the user interaction part, basic modules deal with synthesizing text into dialogs. Other two modules have been developed to link the robot tasks to the application scenarios defined in the project: (1) the social navigation module (34), which is used to make the robot autonomously approach the users, following methodologies in line with social behaviors and (2) the dialogue module, providing motivational statements based on the context and data collected during the dance session, which will be sent to the underlying speech synthesis module for vocal interaction.

#### Let's Dance Game

Let's dance is a game based on Irish dancing sessions. It has been designed to be intuitive and easy to use for both the patient and the physical therapist. After selecting a difficulty level, players are presented as dancers on the screen, along with footprints that suggest the movement to be done.

Each task can vary from simple aerobic exercises (side steps, arm raising, hand-clapping, etc.) to choreographies.

Preliminarily to the use of the game, warm-up exercises will be proposed, in order to minimize physical problems related to the execution of dance steps. After the warm-up, the therapist will log in, will select the involved patients, and will choose the first song and level to be performed. At the end of the dance session, cool-down exercises will be carried out in order to restore the resting condition.

The complexity of the step sequence may increase, ranging from simple steps interspersed with pauses, to sequences of steps, up to complete choreographies, based on the dance movements in the Irish style and Irish music.

An example of steps that will be used: rest, step forward right or left foot, step backward right or left foot, side-step right or left, fake step forward right or left foot, fake step backward right or left foot, full lift right or left arm, partial lift right or left arm.

#### Wearable Wellness System Sensorized Shirt

During the rehabilitation session, patients will wear the Wearable Wellness System (WWS) sensorized shirt, produced by Smartex (http://www.smartex.it/it/prodotti/204-wws). WWS offers a high level of comfort that makes it particularly suitable for monitoring physiological parameters even for long periods. The sensorized garment is produced using natural and synthetic yarns and it can be used as underwear.

The shirt is a fully integrated wearable system for the continuous monitoring of physiological parameters, composed of a sensorized undershirt and an electronic board allowing the continuous monitoring of some clinical parameters relevant to the evaluation of the user's stress and physical state. The shirt is composed of:

- a sensorized garment (t-shirt, in different sizes and profiled for female and male silhouette);- an electronic device designed for data acquisition, pre-processing, storage, and transmission;- a customized software for the configuration of the device and the processing, management, transmission of the acquired data.

The system is capable of simultaneously acquiring the following signals:

- ECG signal and- respiratory signal.

The ECG and respiratory signals are obtained through the use of textile-based fiber sensors integrated directly into the structure of the garment.

The processor on board the electronic device elaborates the acquired signals, through sophisticated signal processing algorithms for artifacts/noise reduction and for the real-time extraction of heart and breathing rate values in a reliable way.

The system has been tested to evaluate its duration in number of washes and times of use. The first signs of aging appear after 50 cycles of delicate washing.

#### AI Reasoner

Its role is to realize the reasoning capabilities necessary to contextualize and adapt the behavior of the SI-ROBOTICS system according to the clinical objectives of the session and the “dynamic performance” of the users. During the session, the artificial vision system and the installed physiological sensors will produce a flow of data used by the reasoner to monitor the progress of the session and the status of the users.

The step sequences generated by the reasoner will be sent to the game for the dance session execution. During the exercise, the reasoner's role will be to monitor performance and to dynamically adapt the exercise when necessary.

Generally, there are two types of scenarios that we will consider during the course of the session:

- Complete session: in this scenario, the reasoner will not face any special situations and/or conditions during the exercise.- Interruption or dynamic adaptation of the session: in this scenario, the reasoner encounters abnormal situations that require direct intervention of the system and dynamic adaptation of the session.

Moreover, the reasoner will suggest to the therapist the change from one level of difficulty to another during the treatment, on the basis of variations calculated on patient-specific baseline values taken at the beginning of the intervention.

#### Artificial Vision Setting

As already said, another Intel RealSense depth camera will be installed in the experimental setup and will be used for the extraction of kinematic parameters, thanks to the Skeleton Tracking SDK developed by Cubemos (München, Germany). Indeed, for each detected skeleton, the spatial coordinates (x, y, and z) and the detection confidence of 18 joints will be estimated. For each step involved in the Irish dance subsession, the following clinical key performance indicators (KPIs), agreed with the physiotherapists, will be extracted in real-time:

- step symmetry;- symmetry between left and right foot (computed for lower limbs);- symmetry between left and right arm, with respect to the request, i.e., 90° or 180° lift exercise (computed for upper limbs);- inclination of the trunk: the flexion of the trunk will be measured during the dance. A warning will be triggered if the person tilts the trunk forward exceeding the tolerance.- the center of gravity: the stability of the subject will be evaluated by calculating the position of the center of gravity. The system will give a warning when the projection of the center of mass exits the support base defined by the length and position of the feet.

#### A Middleware to Facilitate Module Interaction

The interoperable platform is intended as a distributed middleware, i.e., a set of protocols, interfaces, and services for the development of applications capable of processing large amounts and streams of data from heterogeneous sources.

For the rehabilitation program, the platform will monitor the values and allow the exchange, and processing of data through artificial intelligence algorithms, thus obtaining information useful to the physical therapist in the evaluation of the patient's performance.

This is possible through the main components internal to the middleware:

Event bus interoperability framework: it allows communication and data exchange between the components through the use of *connectors* and *topics* according to the *publish–subscribe* mechanism (a publisher publishes an event to the Event Bus; on the other hand, the subscriber receives this event).Stream and batch processing for the data analysis in real-time or batch.Persistence layer: it allows the persistence of circulating information.

### Outcomes

All outcomes will be measured following a standardized operating procedure. Table 1 shows the primary and secondary outcomes.

**Table 1 T1:** Outcomes and clinical assessments.

**Outcome(s)**	**Clinical assessment**
Primary: acceptability of the SI-ROBOTICS system	UTAUT
Secondary: gait improvement (increase in walking speed)	Gait speed during 6 MWT though (G-Walk sensor)
Secondary: balance	POMA
Secondary: fear of falling	FES-I Short form
Secondary: general functional status	SPPB and TUG
Secondary: user satisfaction	GAS
Secondary: cardiac and respiratory performance	HR and RR using wearable sensors
Secondary: quality of life	SF-12

*UTAUT, Unified Theory of Acceptance and Use of Technology; 6 MWT,6 Minute Walking Test; POMA, Performance-Oriented Mobility Assessment; FES-I, Short Falls Efficacy Scale – International; SPPB, Short Physical Performance Battery; TUG, Time Up and Go; GAS, Goal Attainment scale; HR, Heart Rate; RR, Respiratory Rate; SF-12, Short Form (12)*.

A summary of all data collected and when these are collected is provided in Table 2.

**Table 2 T2:** Schedule of assessment and outcome measures.

	**R**	**T0**	**T1**	**T2**
Mini Mental State Examination (MMSE)	✓			
Functional Ambulation Category (FAC)	✓			
Rankin Scale	✓			
Hoen and Yahr Scale	✓			
Geriatric Depression Scale−5 items (GDS)	✓			
Socio-demographics check list		✓		
Barthel Index		✓		
Short Form Health Survey (SF-12)		✓		✓
Assistive Device Predisposition Assessment—Scale E (ATDPA)		✓		
Unified Theory of Acceptance and Use of Technology (UTAUT)				✓
Performance-Oriented Mobility Assessment (POMA)		✓	✓	✓
Short Falls Efficacy Scale—International (FES—I)		✓	✓	✓
Short Physical Performance Battery (SPPB)		✓	✓	✓
Unified Parkinson's Disease Rating Scale—III (UPDRS—III)		✓	✓	✓
Timed Up and GO (TUG)		✓	✓	✓
6 Minute walking test (6 MWT)		✓	✓	✓
Goal Attainment scale (GAS)		✓		✓
*Ad hoc* scale on satisfaction with the SI-ROBOTICS intervention				✓

*R, Recruitment; T0, Start of treatment; T1, Mid-treatment (4 weeks); T2, end of treatment (8 weeks). ✓indicates when the test has been performed*.

The scales which will be used during the evaluations are described below.

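### The primary acceptability score (UTAUT) is scheduled only at week 8, with nothing at early stopping, so patients who leave because they reject the system may go unmeasured and acceptability may be overestimated

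*Protocol article*

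**What the plan says.** The Trial Design section describes a single-group study: "The study is designed as a technical feasibility pilot to test the SI-ROBOTICS system on a group of 20 older people with PD". Table 1 (Outcomes) names one primary outcome, "Primary: acceptability of the SI-ROBOTICS system", assessed by UTAUT.

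Table 2 (Outcomes) sets the timing. The row for "Unified Theory of Acceptance and Use of Technology (UTAUT") has a single tick, under T2. The legend defines the later time points as "T1, Mid-treatment (4 weeks); T2, end of treatment (8 weeks"). It lists no visit for patients who stop early. The ad hoc satisfaction scale is also ticked at T2 only. Six functional measures (POMA, short FES-I, SPPB, UPDRS-III, TUG and 6MWT) are ticked at T0, T1 and T2.

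The Intervention section gives the programme: "Sixteen therapy sessions of 50 min will be conducted (two training sessions per week, for 8 weeks), involving two patients at a time". It adds: "Participants will have to complete at least 80% of the sessions". It does not say what follows if a patient falls short.

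The Data Analysis section summarises the UTAUT subscales descriptively. It sets no acceptability threshold.

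**The concern.** In most trials dropout is only sometimes related to the outcome. Here, leaving because one does not want to dance with the robot is itself non-acceptance. If the instrument is given only at the end, the patients most likely to score low are also the most likely to have no score. The summary then describes acceptability among those who accepted the system well enough to stay.

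This is a matter of the stated schedule and not of analysis detail that an article may leave to another document, because a score never collected cannot be restored by an analysis plan. Nothing else in the schedule fills the gap, since the only other acceptability measure has the same timing. A patient who leaves between weeks 4 and 8 would have mid-treatment data on six functional measures and none on the primary outcome. With one group there is also no comparator in which such selection could cancel.

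What is at stake is how far the result can be relied on. The Discussion says a larger study is planned, and this acceptability figure would be a natural input to it.

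**Working it through.** The article states no dropout rate, power or expected UTAUT score, so there is no figure to reproduce. The check covers the attendance rule and the possible size of the selection.

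**Inputs from the article.** 20 patients, 16 sessions (2 per week × 8 weeks), at least 80% attendance, UTAUT at T2 only.

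**Assumed inputs.** The number without a UTAUT score (k of 20), and the gap in mean score between those who complete and those who leave. The article gives no scoring range for UTAUT, so gaps are in points of an assumed 5-point scale.

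**1. Attendance rule.** 0.80 × 16 = 12.8, so at least 13 sessions (13/16 = 81.25%; 12/16 = 75% falls short). At most 3 may be missed. A patient who stops at T1 has had about 8 of 16 sessions (50%) and no scheduled UTAUT up to then.

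**2. Bias of a completers-only mean.** Let d = k/20, with mean score C in completers and L in leavers. The all-enrolled mean is (1 − d)·C + d·L, so

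bias = C − [(1 − d)·C + d·L] = d × (C − L).

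| Lost (k) | d | n scored | gap 0 | gap 0.5 | gap 1.0 | gap 2.0 |
|---|---|---|---|---|---|---|
| 0 | 0 | 20 | 0 | 0 | 0 | 0 |
| 1 | 0.05 | 19 | 0 | 0.025 | 0.05 | 0.10 |
| 2 | 0.10 | 18 | 0 | 0.05 | 0.10 | 0.20 |
| 4 | 0.20 | 16 | 0 | 0.10 | 0.20 | 0.40 |
| 6 | 0.30 | 14 | 0 | 0.15 | 0.30 | 0.60 |

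**3. Comparison with sampling error.** Assume a subscale SD of 1. The 95% half-width is t(0.975, n−1)/√n for the n actually scored.
- 4 lost, n = 16: 2.131/4 = 0.53, against a bias of at most 0.40.
- 6 lost, n = 14: 2.160/3.742 = 0.58, against a bias of at most 0.60.

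In this table the bias passes the half-width only in the most extreme cell, and then barely.

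**4. The same question as a proportion.** Suppose 4 of 20 have no score and 13 of the 16 completers are judged to accept the system. The completers' figure is 13/16 = 81%. Over all 20 it lies between 13/20 = 65% (all 4 reject) and (13 + 4)/20 = 85% (all 4 accept).

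**The case against.** The strongest reply concerns the attendance rule. A reader might infer that anyone below 80% has no UTAUT score, or is dropped from the analysis. The article does not say so. The Intervention section attaches no withdrawal, replacement or exclusion to low attendance, Table 2 does not make T2 conditional on it, and the Data Analysis section does not restrict the primary summary to those who met it. A patient with 10 of 16 sessions who comes at week 8 would complete UTAUT as scheduled. This objection stands, and the point does not rest on the 80% rule.

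A reader might also infer that leavers can never contribute and that the result is biased upward. That too goes beyond the text. T2 is defined by time, and nothing bars asking a patient who has stopped to complete the questionnaire then. Patients may leave for reasons unrelated to the robot, such as illness or the twice-weekly schedule, and such losses need not raise the mean. This also stands, so the claim has to be put as a possibility.

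It can further be said that the analysis set, missing-data rules and the status of the 80% requirement commonly sit in the full protocol or analysis plan. That is right, and their absence from the article is not part of this point. Nor does leaving attendance out of Table 1 contradict a primary aim of acceptability by UTAUT.

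Finally, measuring acceptance after the full programme is a legitimate choice for a descriptive pilot. It is, but it is no reason to omit a measurement at stopping. The objections leave that gap in the schedule untouched.

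**Conclusion.** The point holds in limited form. As scheduled, the sole primary outcome is collected once, at 8 weeks, with no second acceptability measure before then and none at discontinuation. Patients who stop because they reject the system may therefore be missing from the primary summary, and acceptability may be overestimated.

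The size cannot be derived from the article. It is nil if nobody is lost, or if leavers would score the same as completers. The range of 0.025 to 0.60 points rests wholly on assumed losses of 5% to 30% and assumed gaps of 0.5 to 2.0 points; the comparison with sampling error also assumes an SD of 1. It should not be claimed that the bias generally exceeds sampling error.

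This is a worthwhile and inexpensive improvement to a stated schedule. It does not show that the study's result will be wrong.

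**What to change.** - **Table 2:** add UTAUT at the time of any early discontinuation and at the existing T1 visit.
- **T2:** invite every enrolled patient to complete UTAUT at 8 weeks regardless of sessions attended, and state that the 80% requirement does not define the primary analysis set.
- **Reporting:** keep the T2 UTAUT summary as the primary result. Set beside it the scores and stated reasons of those who stopped, and the proportion of all enrolled patients completing at least 13 of 16 sessions, with an exact 95% confidence interval.
- **Last available UTAUT:** do not make this the primary analysis. It carries earlier scores forward and mixes 4-week with 8-week exposure in one mean. At most, use it as a sensitivity analysis.

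The cost is a few minutes of questionnaire time, mostly at a visit that already exists, with no extra patients and no change to the intervention. Repeating the questionnaire may have a small effect on later answers, and the acceptability figure may come out less favourable.
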